# Handling of Personal Information

Persons involved in research shall comply with applicable laws and ordinances regarding the protection of personal information of research subjects. In addition, the relevant parties shall make every effort to protect the personal information and privacy of the research subjects, and shall not divulge personal information obtained in the course of conducting this research without a justifiable reason. The same shall apply even after the person concerned has retired from the position.

The data will be managed as personal information after changing the name to a research number. Information that can restore personal information (so-called correspondence table) is managed by the personal information manager on a PC that is not connected to the Internet.

# Burdens and anticipated risks and benefits to the study subjects

## Burden and anticipated risks to research subjects

This study is not applicable because it is not invasive.

## Expected benefit to the study subject

Receiving nutritional guidance can be expected to reduce serum potassium levels, resting blood pressure, and urine protein up to 3 months after the intervention compared to before the intervention.

## Comprehensive evaluation of these and measures to minimize burdens and risks

Not applicable.

# Methods of storage and destruction of samples and information

The information obtained in this study will be stored in a locked archive of the Department of Pharmacy, Mie Chuo Medical Center. In addition, insurance pharmacies also store it in a locked library.

As for the disposal method, after the period of time until the date of 5 years from the report of the completion of the study or 3 years from the date of the last publication of the results of the study, whichever is later, the paper media should be shredded and other media should be disposed of in an appropriate manner.

Researchers shall confirm that appropriate procedures are being followed by the person providing the sample or information, and shall prepare a record of the provision of the sample or information. The Principal Investigator shall retain the records prepared by the Researcher for a period of five years from the date of the report of the completion of the study or three years from the date of the last publication of the results of the study, whichever is later. The principal investigator shall keep documents related to the conduct of the research (copies of application documents, notification documents from the hospital director, copies of various applications and reports, lists of research subject identification codes, consent forms, case reports, etc., and other documents or records necessary to guarantee the reliability of the data, etc.), and on the date on which five years have elapsed from the report of the completion of the research. Alternatively, anonymized materials will be discarded after the period of time until the date of the last publication of the research results, whichever is later, has elapsed.

# Contents and methods of reporting to the head of the research institute

The reporting method shall be in accordance with the regulations of each organization.

## Reports from Researchers

Researchers shall report to the head of the research institution in the following cases.

- When serious concerns arise from the viewpoint of respecting the human rights of research subjects, etc., or from the perspective of conducting research, such as leakage of information related to research.
- When facts or information that impairs or may damage the appropriateness of the conduct of research or the credibility of research results are obtained.

## Report from the Principal Investigator

The principal investigator shall report to the head of the research institute in the following cases. In line with this, we will consider suspending or discontinuing the research and changing the research protocol as necessary.

- When facts or information that impairs the ethical validity or scientific rationality of the research, or information that may be impaired and is considered to affect the continuation of the research, is obtained.
- When facts or information that impairs or may damage the appropriateness of the conduct of research or the credibility of research results are obtained.
- Research Progress
- Incidence of adverse events associated with the conduct of the study
- End of study (including in case of discontinuation) If you do. Prepare and report a report on the completion of the study with a summary of the results.

## Report from the Auditor

It is not applicable because it is not audited.

# Conflicts of interest related to research, such as sources of funding for research

There are no companies that fall under the category of conflict of interest. He is currently applying for the Japan Pharmacists Association's Pharmacist Professional Skills Promotion Research Grant Project.

# How to disclose information about research

This study will be registered in jRCT before the start of the study. The results of this research shall be attributed to the principal investigator. The principal investigator, co-investigator, and statistical analyst will discuss and select the authors and report them at academic conferences or papers. Results will not be disclosed to study subjects.

# Responding to consultations from research subjects and related parties

The Research Secretariat will serve as a point of contact for consultations from research subjects and their related parties.

# Procedures for Obtaining Informed Consent from a Substitute, etc.

"Ethical Guidelines for Life Science and Medical Research Involving Human Subjects" Guidance Chapter 4 Informed Consent, etc. Chapter 9 Procedures for Obtaining Informed Consent from Agents, etc. 2 Regarding the "Policy for Selecting Substitutes, etc.," in general, it is basic to select a Representative from among the persons listed in (1) to (3) below.

(1) A person with parental authority or a guardian of a minor (if the research subject is a minor)

(2) Spouses, parents, siblings, children, grandchildren, grandparents, relatives living together, or persons who are considered to be equivalent to their close relatives (excluding minors) ）

(3) A representative of the research subject (including a voluntary guardian who has been granted the right of representation) ）

However, it is desirable that the applicant be selected not uniformly, but rather that a person who is considered to be able to represent the will and interests of the research subject is selected after taking into account the circumstances of each research subject, such as the mental joint relationship such as a partnership or relationship of trust with the research subject, and in some cases the possibility of abuse of the research subject. In addition, when informed consent is received from a substitute, it is also important to keep a record showing the relationship between the substitute and the research subject.

# Procedure for obtaining an informed ascent

The study is for adults 18 years of age and older, subject to the patient's voluntary participation, so ascent is not required.

# Statement of financial burden or gratuity of research subjects, etc., and their details

The present study will be conducted within the normal scope of practice. For this reason, the medical expenses incurred by the study subjects are carried out using the health insurance of the researchers. Participants in this study will not be responsible for transportation expenses or honorariums.

# Response in the event of a serious adverse event

Adverse events that occur within 84 days of the start of the protocol will be followed up until the adverse events improve.

Emergency Reporting

1) The principal investigator/co-investigator will take appropriate measures in the event of a serious adverse event. The co-investigator shall immediately report to the principal investigator, regardless of the causal relationship with the study drug.

2) The Principal Investigator shall immediately report the serious adverse event to the head of the medical institution and notify the Investigator of the Drug Provider. In addition, it will be reported to the Effectiveness and Safety Evaluation Committee as necessary.

3) The report format and procedures for adverse events and adverse events for which a causal relationship with the study drug cannot be ruled out shall be in accordance with the "Procedures for Serious Adverse Events (established by each institution)".

< Emergency Contacts>

Principal Investigator: [name]

Department of Pharmacy, Mie Chuo Medical Center

[name]

[contact] [contact] (Pharmacy Department)

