# Method and duration of the study

## Study design (research method)

・Case registration

CKD severity classification stages G3b, G4, G53^)^

When the outpatient prescription of the Mie Chuo Medical Center is brought to the insurance pharmacy, the written consent of the patient is obtained and registered. The date of obtaining consent shall be Day 1.

・Intervention method

All of the following interventions are performed by pharmacists at insurance pharmacies.

Date of Obtaining Consent (Day 1)

1. Questionnaire of the Awareness Survey on the Intake of Potassium-Containing Foods in Patients (Questionnaire 1) Appendix 2

2. Dietary guidance: Guidance on nutritional guidance for CKD (Annex 1) will be used. (Recommendation of nutritional guidance to the Nutrition Management Office as necessary)

3. Measurement of resting blood pressure after the visit

4. Provision of information to the Mie Chuo Medical Center on the status of the administration of potassium adsorbents: If the cause of poor adherence is the dosage form or dosage, the information will be provided to the Mie Chuo Medical Center of the prescriber in a tracing report.

⇒ hospital pharmacist writes details such as dosage status on the bulletin board of the electronic medical record to the prescribing physician and proposes a dosage change.

Day1-83

1. Dietary guidance (as appropriate)

2. Measurement of resting blood pressure after the visit

3. Confirmation of the status of potassium adsorbents (if information is provided to Mie Chuo Medical Center, confirmation of dosage type change, etc.)

After Day 84 (end date of the observation period)

1. Questionnaire on the Awareness Survey on the Intake of Potassium-Containing Foods by Patients (Questionnaire 2) Appendix 3

2. Measurement of resting blood pressure after the visit

3. Confirmation of the status of potassium adsorbents (if information is provided to Mie Chuo Medical Center, confirmation of dosage type change, etc.)

Contents of the questionnaire

For all questions, set a five-level answer.

At the time of obtaining consent (Day 1): Questionnaire 1

Q1. Do you know that potassium in the blood should not be too high?

Q2. Do you know of any foods that contain a high amount of potassium?

Q3. Are you conscious of refraining from foods that contain a lot of potassium?

Q4. Is it annoying (troublesome) to be aware of potassium intake?

3 months after obtaining consent (after Day 84): Questionnaire 2

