## Research Period

Registration Period: From the date of permission (or the date of publication of the RCT) to February 28, 2023

Study Period: From the date of permission (or the date of publication ofthe J RCT) to May 31, 2023

Duration of participation: 6 months

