## Observation items and methods

### Observations and information and samples to be collected

The blood and urine test data used in this study will not be newly tested because the data obtained in daily practice will be obtained retrospectively (retrospectively) through electronic medical records.

(Pre-intervention)

- Patient background: age, gender, body mass index, medical history (heart failure, diabetes), how to manage medications at home (family management or self-management), meals at home (self-catering, home delivery, eating out)
- Blood tests: serum albumin level, Na, Cl, K, Mg, aspartate aminotransferase, alanine aminotransferase, eGFR, blood urea nitrogen, red blood cell count, white blood cell count, Hemoglobin level, hematocrit, platelet count
- Urinalysis: urine albumin, urine albumin/creatinine ratio, or urine protein, urine protein/creatinine ratio
- Oral medications: presence or absence of concomitant medications (mineralocorticoid receptor antagonists, renin-angiotensin-aldosterone inhibitors, sodium glucose cotransporter2 inhibitors) that increase serum potassium levels, presence or absence of concomitant medications (loop diuretics) that reduce serum potassium levels, presence or absence of potassium adsorbents
- Vitals: Resting blood pressure (systolic and diastolic) after visiting the station

In addition, if the blood pressure at home is recorded in the blood pressure notebook, it is possible to substitute the resting blood pressure after the visit.

(12 weeks after intervention)

- Patient background: age, gender, body mass index, medical history (heart failure, diabetes), how to manage medications at home (family management or self-management), meals at home (self-catering, home delivery, eating out)
- Blood tests: serum albumin level, Na, Cl, K, Mg, aspartate aminotransferase, alanine aminotransferase, eGFR, blood urea nitrogen, red blood cell count, white blood cell count, Hemoglobin level, hematocrit, platelet count
- Urinalysis: urine albumin, urine albumin/creatinine ratio, urine protein, urine protein/creatinine ratio
- Oral medications: presence or absence of concomitant medications (mineralocorticoid receptor antagonists, renin-angiotensin-aldosterone inhibitors, sodium glucose cotransporter2 inhibitors) that increase serum potassium levels, presence or absence of concomitant medications (loop diuretics) that reduce serum potassium levels, presence or absence of potassium adsorbents

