### Observation and Reporting Schedule

| item | Prescription Fulfillment  (Start of observation) |  |  | End of Observation Period |
| --- | --- | --- | --- | --- |
| Number of days elapsed since obtaining consent | Day1 |  |  | Day 84 onwards* |
| Obtaining Consent | 〇 |  |  |  |
| Questionnaire for awareness survey on the intake of potassium-containing foods | 〇  (Questionnaire 1) |  |  | 〇  (Questionnaire 2) |
| Nutritional Guidance on Potassium Restriction | 〇 |  |  | 〇 |
| Follow-up on Nutrition Guidance |  | 〇 | 〇 |  |
| Patient Background Verification | 〇 |  |  | 〇 |
| Checking blood test data | 〇 |  |  | 〇 |
| Confirmation of urinalysis data | 〇 |  |  | 〇 |
| Confirmation of oral medication | 〇 |  |  | 〇 |
| Measurement of resting blood pressure after the visit | 〇 | 〇 | 〇 | 〇 |
| Confirmation of adherence of potassium adsorbents | 〇 | 〇 | 〇 | 〇 |

*The date of data acquisition after 84 days after obtaining consent depends on the date of the patient's outpatient treatment, so it shall be after Day 84.

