## Predictable adverse events

Nutritional guidance on potassium restriction may cause hypokalemia.

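### The 84-day adverse-event window closes at or before the only post-guidance potassium check, so follow-up of hypokalaemia first found there is not clearly covered

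*Protocol*

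**What the plan says.** - **Window.** Protocol section 17 (Response in the event of a serious adverse event), repeated word for word in 17.3 (Emergency Reporting): "Adverse events that occur within 84 days of the start of the protocol will be followed up until the adverse events improve". No other adverse-event text in the protocol carries a date limit.
- **Predicted harm.** Section 17.2 lists one item: "Nutritional guidance on potassium restriction may cause hypokalemia".
- **Blood data.** The schedule in 3.6.2 marks the check of blood results at Day 1 and at the end of observation, and leaves the two columns between empty. The end column is headed as Day 84 onwards. Its footnote says that the date "depends on the date of the patient's outpatient treatment, so it shall be after Day 84". No latest date is given.
- **Source.** Under 3.6.1, blood and urine results "will not be newly tested because the data obtained in daily practice will be obtained retrospectively". The study orders no test of its own.
- **Between the two checks.** Section 3.1 lists guidance, blood pressure and potassium-adsorbent status for Day 1 to Day 83, but no potassium value.
- **Clock.** Section 3.1: "The date of obtaining consent shall be Day 1".
- **Other reporting.** Section 3.6.3 requires a six-monthly report of adverse events to the hospital director. Section 10.2 has the principal investigator report their incidence. Neither has an 84-day limit.
- **Limit for low potassium.** The exclusion criteria (4.1.2) treat a serum potassium below 4.0 mmol/L as hypokalaemia. No section adopts that figure as an adverse-event limit.

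**The concern.** Hypokalaemia is recognised chiefly from a laboratory value. If the one planned look at that value comes when the dated window has already closed, the rule for following events until they improve does not plainly apply to the harm the protocol expects.

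The primary analysis does not fill the gap. It compares mean potassium before and after guidance, and a lower mean is the intended benefit. The mean can move in the desired direction while individual patients drop too low, and nothing in the stated analysis counts them. What is at stake is the follow-up of those patients and a clear account of the one harm named. The primary test itself is unaffected.

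**Working it through.** The plan states no figure to reproduce on this point. The check is a comparison of windows, followed by an illustration.

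**1. Inputs.** Day 1 is the consent date (3.1). Recruitment runs from 1 December 2022 to 28 February 2023 (4.2). The study period ends on 31 May 2023 (3.3). Assumption: the undefined start of the protocol in section 17 means Day 1 for each patient.

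**2. Dates.** Day 84 = consent date + 83 days. The study day of 31 May 2023 = (31 May 2023 − consent date) + 1.

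| Consent | Day 84 | 31 May 2023 is | Days from Day 84 to study end | Possible days for the end check |
|---|---|---|---|---|
| 1 Dec 2022 | 22 Feb 2023 | Day 182 | 182 − 84 = 98 | Day 84 to 182, that is 99 |
| 28 Feb 2023 | 22 May 2023 | Day 93 | 93 − 84 = 9 | Day 84 to 93, that is 10 |

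**3. Overlap.** The window ends on Day 84 if days are numbered from consent as Day 1, or on Day 85 if 84 full days are counted after consent. The end check opens on Day 84 by the column heading, or on Day 85 by the footnote read literally.

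| | Check opens Day 84 | Check opens Day 85 |
|---|---|---|
| Window ends Day 84 | 1 day | 0 days |
| Window ends Day 85 | 2 days | 1 day |

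So 0 to 2 of the 99 (or 10) possible days fall inside the window.

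**4. Illustration only.** The protocol does not give the baseline distribution of potassium, so these inputs are assumed: baseline normal with mean 4.5, 4.7 or 4.9 mmol/L and SD 0.5; correlation 0.6 between baseline and end values; entry only at 4.0 mmol/L or more. The end value is simulated as mean + 0.6 × (baseline − mean) − fall + error, with error SD 0.5 × √(1 − 0.6²) = 0.4. The table gives the share of patients below 4.0 mmol/L at the end, with the count out of 40 in brackets.

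| Fall in mean | Mean 4.5 | Mean 4.7 | Mean 4.9 |
|---|---|---|---|
| 0 (no effect) | 10% (4) | 6% (2) | 3% (1) |
| 0.25 | 24% (10) | 15% (6) | 8% (3) |
| 0.5 | 43% (17) | 30% (12) | 19% (8) |

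The 0.5 row matches the difference used in the sample-size rationale (3.2.2), which the protocol itself describes as an upper figure from earlier work. The zero row shows what within-patient variation alone would produce. The counts use the exclusion limit of 4.0 only because it is the one limit the protocol prints.

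**The case against.** The strongest reply is that section 17 sets a follow-up rule and not a limit on recording. A reader might infer that hypokalaemia falls outside the safety record, or that the trial could report no adverse events despite low values in its own data. The documents do not support that:

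- Sections 3.6.3 and 10.2 require adverse-event reporting without a date limit, and the serious-event reporting steps in 17 and 17.3 have none either.
- The rule turns on when an event occurs. A low potassium that arose during the 84 days and was found later may still qualify.
- The schedule says when the study reads the record, not when blood is drawn. Routine results, or symptoms, before Day 84 may reveal a case.
- The end potassium is kept as the primary endpoint, so low values can be counted afterwards.

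All of this stands and narrows the point. It does not close the gap. The institutional reports set no window for collection, and the protocol does not say how onset is to be dated when a low value first appears at the end check.

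A reader might also see a further contradiction in "Duration of participation: 6 months" (3.3). That is not supported: Day 182 is about six months, so the figure fits a maximum length of participation.

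Nor is the absence of an adverse-event row in the schedule, or of an adverse-event field among the listed web-form items, an error. Section 17 refers report format and procedures to each institution's own procedures, which are not shown.

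**Conclusion.** The point holds in a limited form. The only dated adverse-event window closes at or before the only post-guidance potassium check in the schedule, with an overlap of 0 to 2 days. That check may come up to 98 days after Day 84 for the earliest registrant and up to 9 days after for the latest. Hypokalaemia first found there is not clearly covered by the follow-up rule.

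This rests on reading the start of the protocol as Day 1 and on 31 May 2023 as the last possible date. It does not rest on the simulation. The simulated counts (8 to 17 of 40 for a fall of 0.5, 3 to 10 for 0.25, against 1 to 4 with no effect) depend on assumed inputs and on a limit taken from the exclusion criteria. They show only that values below 4.0 mmol/L at the end check are plausible, and they must not be read as a forecast of adverse events. The primary analysis is unaffected. This is an inexpensive improvement in how safety is captured.

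**What to change.** 1. In sections 17 and 17.3, run the adverse-event window from Day 1 up to and including the end-of-observation blood test, and say that the start of the protocol means Day 1 if that is intended.
2. Reconcile this with the schedule and its footnote (3.6.2), the reporting duties in 3.6.3 and 10.2, and the predicted harm in 17.2.
3. State in advance the potassium limit that the sponsor will use for hypokalaemia as an adverse event. The choice is the sponsor's; the protocol gives below 4.0 mmol/L only as an exclusion limit.
4. From the electronic records already being read, report beside the primary result the number of patients with any recorded potassium below that limit from Day 1 to the end-of-observation test. Values below the limit are expected even without an effect, so the count needs that context.

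The cost is a few lines of wording and a slightly larger record extraction, because potassium results between Day 1 and the end test must also be listed. No new blood test is needed. The adverse-event count may look less favourable.

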## Serious adverse events

Adverse events that fall under any of the following are considered "serious adverse events".

1. What leads to death
2. Life-threatening
3. Those that require hospitalization for treatment or extension of the length of hospitalization
4. Permanent or significant disability or malfunction
5. What causes birth defects in offspring

"Unpredictable serious adverse events" means serious adverse events that are not described in the study plan, explanatory documents of informed consent, etc., or that are described but whose nature or severity does not match the description.

